### Data collection/interviews

To collect data for the third and fourth aims, interviews will be conducted in the middle of the intervention (at 6–8 weeks) and at the 12-weeks follow-up.

The interviews of the residents will be collected in a secluded locality in the participants´ homes within the NH. Each person interviewed will be asked to describe how he/she perceived the experience daily being offered to conduct the STS exercise and to drink the nutritional supplement (with support of staff). A special focus will be held on questions concerning health, wellbeing and independence. Interviewing persons with memory impairment has been suggested to be potentially problematic [46].

A common problem is that persons with dementia might have difficulties recalling answers to specific questions and staying on subject. Furthermore, a common argument is that the memory loss is not static, which means that the person with dementia sometimes remembers more aspects on a topic than at other times [47]. Inclusion of persons with dementia in interviews is suggested feasible although the memory can fail in some detail. For example, Wikström [48] proved this to be a fruitful method, finding that a complex picture of the interviewees’ perceptions became visible. To discover each person’s unique, individual descriptions, they suggest to interview the participants separately. From an ethical viewpoint, this also seemed a fair approach for all older participants, since they in that way are equally acknowledged by the researcher.

In a similar vein to the interview questions for the residents above, interviews on the same topic will be posed to staff in the NH’s. Here, a focus group methodology will be used [49, 50]. The strength of a focus group methodology is that the group is viewed to facilitate and enable respondents to share experiences, that in turn will feed in to- or trigger- the memories of others, that will be able to share more in-depth thoughts and ideas. The interviews will be conducted in groups of 3–5 staff, and will be tape-recorded [51, 52]. The interviewees will describe their perceptions of promoting the STS exercise and the intake of the nutritional supplement with the NH residents, including e.g. experienced barriers and strategies to overcome them, but also on the residents’ health, wellbeing and independence.

The interviewer will not interrupt unless the interviewee indicated that he/she had finished elaborating on a topic, or if a follow-up question was of interest to reach further depth in the descriptions. Sometimes, however, the participants might need to be reminded of the researcher’s focus of interest, which will be done by interruption and a repetition of the question. The time the participants will use to describe their perceptions and experiences of the OPEN project on their health and wellbeing will approximately range from 20 to 50 min.

Interview guides for the individual interviews and the focus group interviews will be developed. Field notes on aspects that might affect the perceptions of the sit-to stand activity told either by the participants themselves or the staff will be written down in immediate conjunction to the interviews [53].

### Data collection procedure

When a resident has accepted to participate, the data collection will be performed by two clinically experienced physiotherapists from the research group at baseline and at follow-up. The data will be collected at the participating NH’s. Assessments will take place in the participant’s room and in the facilities outside the room (i.e. the corridor for the walking test). The assessors will discuss the tests before study start to ensure high reliability of assessments. Blood samples will be collected and handled by 2 persons experienced in collecting and handling blood samples not routinely used in nursing homes. Demographic data will be retrieved from patient records with access help from the ward nurses.

Interviews with staff and NH residents will be performed by a researcher with great experience of qualitative research and interviewing older persons and staff.

Enrolment to the study will be ongoing until 120 participants, 60 in each group, are included.

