### Participants

Residents aged ≥75 years living in NH’s in the two municipalities will be invited to participate. Screening of all residents in the participating NH according to inclusion and exclusion criteria will be conducted by ward nurses and physiotherapists in cooperation with research staff. Eligible subjects will then be approached in person by the research staff for verbal informed consent. Information about the study will be given both in oral and written form.When needed, the research staff will read the written information loud to the older person.

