#### Exclusion criteria

Persons with a Body Mass Index (BMI) > 30, treated with protein-rich oral supplement, suffering from severe dysphagia, tube fed, bedridden, severe kidney disease, at a terminal stage of life, lack of informed consent will be excluded. Resident who by the responsible nurse is assessed as not eligible to participate due to psychological or cognitive reasons will also be excluded. Psychological reasons is defined as anxiety and/or risk for increased behavioral problems due to something new added to the person’s daily life. Cognitive reasons is defined as not be able to follow instructions.

Among the older persons who have accepted participating in the intervention group, approximately 20 persons will be invited to participate in individual interviews. This is a number estimated to secure data saturation, which is strived for in Grounded theory methodology [29].

Staff, who will support the residents to complete the intervention, will be invited to participate in the qualitative part of the study. Staff will be recruited for interviews by convenience sampling, although with the criteria that they had experience of having supported residents with the intervention (STS and nutritional supplement).

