### Data collection/outcomes

The quantitative data will be collected at baseline and at the 12-week follow-up. An overview of the data collection is presented in Table 1. The following assessments will be performed to follow variables related to the primary and secondary aims for the study:

**Table 1 Tab1:** Participant timeline

	Enrollment	Allocation	Postallocation		
TIMEPOINT	*-t* _*1*_	0	*t* _*1*_ *baseline*	*t* _*2*_ *intervention*	*t* _*3*_ *w 13*
ENROLLMENT:					
*Eligibility screen*	X				
*Informed consent*	X				
*Information to staff and next of kin*	X				
*Identification of* *“key-persons” and meetings together with representatives from the research group*		X	X	X	X
Allocation		X			
INTERVENTIONS:					
*Sit-to-stand*				X	
*Oral supplementation*				X	
ASSESSMENTS:					
*Sit-to-stand*			X		X
*Functional balance*			X		X
*Walking ability*			X		X
*ADL*			X		X
*Nutritional status*			X	X subgroup	X
*Health related quality of life*			X		X
*Healthcare resource use*			X		X
*Demographic data*			X		
*Medical incidences*				X	X
*Interviews of residents*					X
*Interviews of staff*				X	X

t_1_ baseline, t_2_ intervention period of 12 weeks, t_3_ 12 weeks follow up

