### Sample size calculation

The sample size calculation for the number of participants is based on the effect size of the primary outcome measure in a pilot study performed and described in a study protocol by a Canadian research group that we collaborate with [24]: that is the number of sit-to-stands that the participant is able to complete in 30 s. An increase of 2 sit-to-stands completed in 30 s is suggested to be a meaningful change in the person’s mobility. Based on existing research [30, 43–45] the standard deviation of the 30-s sit-to-stand measure is 3.5 sit-to-stands. Based on the power calculation by Slaugther and colleagues [24], 49 participants in each group are needed to detect an increase in the number of sit-to-stands (power = 0.80; 2-tailed; α = 0.05). Assuming an attrition of 20% over the 12 weeks, we will recruit in total 120 participants (60 participants to each group).

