### Data collection procedure

Residents living in Swedish NH’s today are frail and vulnerable and a rapid decrease in length of stay between 2006 and 2012 has been reported. The most dramatic change was an increase in the proportion of people who moved into an institution and died shortly afterwards [56]. This will probably result in a prolonged recruitment process to the study. A pilot study was performed at one NH with 81 residents to test the study protocol and its feasibility. Some changes were made in the protocol regarding exclusion criteria. The cut off for BMI was raised from 28 to ≤30 and Mini Mental State Examination will be used [40] to assess and describe cognitive function instead of Short Portable Mental Status Questionnaire [57].

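### Table 1 schedules the baseline chair-rise test after cluster allocation with unblinded assessors, and the enrolment rule leaves open whether residents can join clusters whose arm is already known

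*Protocol article*

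**What the plan says.** **Order of events.** In Table 1 (Data collection/outcomes), eligibility screening, consent and information to staff and next of kin fall at −t1. Allocation falls at time 0. The baseline column t1 is the first of the columns headed "Postallocation". All baseline assessments are marked there: sit-to-stand, balance, walking, ADL, nutritional status, quality of life and resource use. The row for identifying and meeting key-persons is first marked at time 0, one column before baseline.

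**Assessors.** Under Data collection procedure (Methods), two physiotherapists from the research group carry out the assessments at baseline and follow-up once a resident has agreed to take part. The Blinding section calls assessor blinding difficult under the cluster design, plans none, and says that clues on the unit or remarks by staff or participants could easily disclose the arm.

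**Enrolment.** The same Data collection procedure section states: "Enrolment to the study will be ongoing until 120 participants, 60 in each group, are included". The Participants section says: "Screening of all residents in the participating NH according to inclusion and exclusion criteria will be conducted by ward nurses and physiotherapists". Research staff take part in this screening. Under Exclusion criteria, the responsible nurse may exclude a resident on psychological grounds, defined as anxiety and/or "risk for increased behavioral problems due to something new added" to the person's daily life. That section also describes the interview candidates as residents who agreed to take part in the intervention arm. The Discussion says of short stays and early deaths: "This will probably result in a prolonged recruitment process to the study".

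**The concern.** Cluster randomisation makes the arms comparable only in what is fixed before the arm is known. Two things here may not be.

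The first is the baseline measurement. A count of chair rises in 30 seconds depends on effort and on the encouragement given. If the assessor, the resident or the staff member present knows the arm, the baseline itself can shift by arm. A change score or a baseline-adjusted analysis then carries that shift into the estimated effect.

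The second is who is enrolled. If residents can be identified after a cluster's arm is known, consent and nurse-judged exclusion could differ between arms. The criterion about reacting to something new may weigh more heavily on a unit that is about to receive the intervention. Neither intention-to-treat analysis nor a random effect for cluster corrects this.

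**Working it through.** **1. The plan's own figure.** Inputs from Sample size calculation: a difference of 2 rises ("An increase of 2 sit-to-stands completed in 30 s is suggested to be a meaningful change in the person’s mobility"), SD 3.5 ("the standard deviation of the 30-s sit-to-stand measure is 3.5 sit-to-stands") and "power = 0.80; 2-tailed; α = 0.05".

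n per group = 2 × [3.5 × (1.960 + 0.842) / 2]² = 48.07, rounded up to 49. This matches the stated 49. For 20% attrition, 49 / 0.8 = 61.25, so 62, or 49 × 1.2 = 58.8, so 59. The stated 60 lies between the two. The present point does not alter this figure.

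**2. Baseline timing.** The sequence in Table 1 is:

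- −t1: screening, consent, information to staff
- 0: allocation; key-person identification and meetings begin
- t1: baseline, including the primary outcome measure
- t2: intervention
- t3: follow-up

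The Intervention group section defines key-persons as staff chosen to facilitate during the intervention, so choosing and meeting them can itself signal the arm. With no assessor blinding planned, nothing in the schedule keeps the arm from those present at t1. No inference is needed to place baseline after allocation. That the arm is known at that moment is possible, not stated.

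**3. How a distorted baseline reaches the result.** Let δ be the difference between arms (intervention minus control) in measurement error at baseline caused by knowing the arm.

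- Analysis of change: the estimated effect is shifted by −δ.
- Analysis adjusted for baseline with slope β: the shift is −βδ.
- Follow-up compared without using baseline: no shift from this source.

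With a slope above zero, adjustment brings the distortion in rather than taking it out. Data analyses specifies mixed models with a cluster random effect. It does not fix how baseline enters, which an article may leave to the analysis plan. Neither the sign nor the size of δ can be had from the document.

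**4. Scale only, on assumed values.** Take 60 × 0.8 = 48 completers per arm, SD 3.5, no true effect and no clustering. The standard error is 3.5 × √(2/48) = 0.714. If a bias of b rises remained in the final difference, the two-sided 5% error rate would be 1 − Φ(1.96 − b/0.714) + Φ(−1.96 − b/0.714):

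| Assumed b | Error rate |
|---|---|
| 0.25 | about 6% |
| 0.5 | about 11% |
| 1.0 | about 29% |

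These values of b are hypothetical. They show how sensitive the test is and do not estimate the bias in this trial. Clustering would enlarge the standard error and make the inflation smaller.

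**5. Enrolment passages side by side.** Table 1 has consent before allocation. The enrolment rule counts residents within each arm, and the interview text speaks of agreeing to take part in the intervention arm. Two readings fit:

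- (a) whole clusters are added, each screened and consented and only then allocated, until the target is met;
- (b) enrolment stays open in clusters already allocated.

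Under (a) selection is protected. Under (b) it is not. Trial design puts clusters at roughly 15–38 persons, so whole clusters would reach exactly 60 per arm only by chance. That makes (b) a natural question but does not establish it.

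**The case against.** The strongest reply is that a reader might infer that residents are selected with the arm known, and the article does not say so. Table 1 puts screening and consent before allocation. The enrolment sentence is a stopping rule that reads equally well as adding whole clusters in turn, and with 62 units available that is plausible. Prolonged recruitment fits both readings, and the sentence about the interview sample does not date consent. This stands: selection after allocation is a possibility that the wording leaves open.

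A reader might also infer that one arm could go on opening clusters after the other has stopped. Nothing supports that. Trial design says only that a computer-based list allocates clusters.

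The exclusion criterion is also not empty on a control unit. Control residents meet visiting physiotherapists, functional tests and blood sampling, and research staff share in the screening. If screening precedes allocation, the mechanism does not arise.

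Finally, some of the clues named under Blinding, such as bottles and reminders, appear mainly once treatment is running, and the timing of disclosure to staff is a detail that a full protocol may hold. The first part limits how sure one can be that the arm is known at baseline. The second does not remove the point, because the article itself fixes the order in Table 1 and counts enrolment by arm.

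**Conclusion.** The point on baseline stands. Followed as written, Table 1 measures the primary outcome's baseline after allocation and after key-person activity has started, with no blinding of assessors, so an effort-dependent measure is exposed to knowledge of the arm.

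The point on selection stands only as an inconsistency to reconcile: the order in Table 1 against an enrolment rule and an interview sentence that can be read as entry to a known arm. It should not be reported as enrolment after allocation.

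The size of any bias cannot be estimated from the document. A figure for the selection effect would need an excess exclusion rate and its correlation with chair rises, and the document gives neither. The conclusion assumes that no fuller document withholds allocation until baseline is complete. If one does, Table 1 and the enrolment sentence still need correcting to agree with it.

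**What to change.** - For each cluster, complete screening, consent and baseline assessment before that cluster's allocation is disclosed to unit staff, residents or assessors.
- In Table 1, move t1 ahead of allocation and mark key-person identification and meetings only after baseline.
- Reword the enrolment sentence so that recruitment proceeds by whole clusters to about 120 in total, with no resident added to a cluster after disclosure.
- Bring the interview-sample sentence under Exclusion criteria into line with consent given before the arm is known.

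Paired or blocked randomisation is not needed for this and would change the allocation scheme.

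The cost is a short delay in each cluster before allocation and training, and arm sizes that may differ somewhat from 60. Because late arrivals could no longer be added, an additional cluster from the 62 units may be required. The change protects baseline and selection only. Unblinded assessment at follow-up remains a separate limitation.

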### Blinding

The blinding of assessors was determined to be challenging to achieve due to the cluster design. Clues in the environment (lists, reminders, bottles) and risk of accidental information given by participants and/or staff could easily reveal the unit’s group assignment.

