### Intervention

#### Intervention group

The intervention period will last for 12 weeks and the participants in the intervention group will perform the STS exercise, where the older person will get up from a chair to stand and then sit down again repeatedly for 1–10 times at each session depending on the participant’s ability, at least four times per day, seven days a week. The exercise will take place in conjunction with daily activities for the older person such as dressing, toileting or at transfers, and be supported by trained staff. The staff will document in a flow chart how many times per day the participant completes the activity.

The staff will be educated about the objectives of the study, and the STS exercise, at group meetings at each unit. In cooperation with the unit manager, several “key-persons” in the staff will be identified, in order to be facilitators during the intervention. The physiotherapist, occupational therapist and/or nurse working at the unit will also be asked to encourage and give practical advice to the staff regarding the STS exercise. The key-persons and representatives of the research group will meet during the intervention period. The purpose for these meetings will be to encourage the key-persons and staff to discuss problems with the intervention that might occur.

The participants will also be offered an oral protein-rich supplement (125 ml, 18 g protein which is 24% of Recommended Dietary Intake, 300 kcal) twice a day (between breakfast and lunch and in the afternoon) during 12 weeks (7 days/week). Studies indicate that only between 50 and 65% of the prescribed volume is consumed (23). Therefore, we chose a supplement with low volume and high protein content. The drink will be served in specially designed study glasses, graded in quarters. The staff will register the intake of the supplements on a flow chart designed for this purpose.

Documentation of the daily exercises and nutritional supplements will be checked every week by the key-persons.

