#### Primary outcome

The number of chair rises in 30 s [30] will be the primary outcome for the study.

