### Data management and monitoring

The participants will be given a unique code for identification. All data will be stored in a folder for each participant and the folder will be kept in a locked cabinet at each nursing home during study time. When the study is concluded, or the participant’s drops out, each folder will be stored according to the routines for archives of research material. After baseline and follow up assessments, the data will be registered in SPSS files at a lap-top especially designated for the OPEN study. Back up files will be created and stored. The interviews will be tape-recorded, transcribed and stored according to the routines for archives of research material.

The study is initiated and planned by the research study group with a multi-professional composition (physicians, physiotherapists, occupational therapist, nurse and dietitian).

No interim analyses of the data will be performed. The research group will have access to the final dataset. Each member of the research group will be allowed to share some of the data supervising master or PhD-students who will be involved in the analyses.

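### The Blinding section calls assessor masking challenging and states no partial safeguard, although the 12-week primary outcome depends on encouragement and on what is counted as a rise

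*Protocol article*

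**What the plan says.** All references are to the protocol article.

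- **Blinding.** "The blinding of assessors was determined to be challenging to achieve due to the cluster design". The reasons given are "Clues in the environment (lists, reminders, bottles) and risk of accidental information given by participants and/or staff", which could disclose a unit's arm. The section ends there. It states no measure to reduce these cues and no record of whether an assessor learned the arm.
- **Primary outcome.** "The number of chair rises in 30 s [30] will be the primary outcome for the study".
- **Data collection procedure.** Once a resident has agreed to take part, "the data collection will be performed by two clinically experienced physiotherapists from the research group at baseline and at follow-up". Testing is done in the resident's room and nearby facilities. The two assessors discuss the tests beforehand, with reliability as the stated aim.
- **Intervention group.** "The key-persons and representatives of the research group will meet during the intervention period". The section does not say which members of the group attend.
- **Data management and monitoring.** Each participant's data are in a folder, and "the folder will be kept in a locked cabinet at each nursing home during study time". Data are entered electronically after the baseline and the follow-up assessments.
- **Data analyses.** Outcomes are analysed by intention to treat, using mixed models with cluster as a random effect.

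**The concern.** A 30-second chair-rise count is a test of voluntary performance. The result can move with how firmly the resident is urged on and with whether an incomplete rise is accepted. If the assessor knows the arm, either can differ between arms at follow-up without anyone intending it, and the difference is added to the estimated treatment effect. The Berg Balance scale and walking speed are exposed in the same way.

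The Blinding section gives clustering as the reason masking is difficult. The routes it names, however, are objects on the unit and chance remarks. The objects can be put away for a test visit, and the remarks can be made less frequent. Difficulty is a reason for partial masking with a record of failures, and the section states neither. This point concerns the 12-week measurement only.

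**Working it through.** **1. The plan's own figure.** Sample size calculation gives a difference of 2 rises, SD 3.5, two-sided 5% and power 0.80.

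n per group = 2 × (1.96 + 0.84)² × 3.5² / 2² = 2 × 7.85 × 12.25 / 4 ≈ 48.1, rounded up to 49.

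This agrees with the stated 49, so no figure in the plan is disputed here.

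**2. Precision of the comparison.** With 49 evaluable per group and no allowance for clustering:

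SE = 3.5 × √(2/49) = 0.707 rises.

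An observed difference of 1.96 × 0.707 = 1.39 rises is then significant.

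**3. Effect of an assessor-induced shift b when there is no true effect.**

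P(reject) = 1 − Φ(1.96 − b/SE) + Φ(−1.96 − b/SE).

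The document gives no value for b, so a range is assumed. The last column repeats the calculation with an assumed design effect of 1.45, also not in the document: SE = 3.5 × √(2 × 1.45/49) = 0.851.

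| Assumed b (rises) | Share of the 2-rise target | Error, no clustering | Error, design effect 1.45 |
|---|---|---|---|
| 0 | 0 | 5.0% | 5.0% |
| 0.25 | 1/8 | 6.4% | 6.0% |
| 0.5 | 1/4 | 10.9% | 9.0% |
| 1.0 | 1/2 | 29.3% | 21.7% |

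**4. Whether the planned analysis would correct it.** Suppose every rating in intervention units is raised by b at follow-up. The arm coefficient then estimates the true effect plus b. The random cluster effect allows for correlation within clusters; it cannot separate b from the treatment effect, because b varies with arm exactly as treatment does. Intention to treat does not address it either.

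**5. Whether the stated reason rules out every safeguard.**

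- Lists, reminders and bottles are movable objects.
- Remarks by staff or residents can be reduced by asking, though not eliminated.
- Contact between assessors and intervention staff through the research group is a matter of assigning roles, which clustering does not determine.

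None of the three is made unavoidable by allocating whole units.

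**The case against.** The strongest reply is that the protocol discloses a real limitation and gives a sound reason for it. The section says that "risk of accidental information given by participants and/or staff could easily reveal the unit’s group assignment", and with clusters of 1–3 units a single remark can unmask the assessor for everyone there. Residents do the exercise at least four times a day for 12 weeks, and 34 of the 62 units are dementia care, so asking residents to stay silent will often fail. All of this stands. It limits what masking can achieve, but it does not show that nothing is worth doing.

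A second reply is that a condensed article may leave rotas, meeting attendance and test scripts to a fuller document. That also has force, and it is why silence on those details is not the point here. The point rests on what the article does set out: a judgement on masking, with its reasons, followed by no safeguard.

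A third reply is that experienced assessors discuss the tests beforehand. That helps the two agree with each other. It does not stop both from leaning towards the same arm.

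A reader might infer more than the document supports:

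- **That masking is abandoned altogether, or that assessors will certainly know the arm.** The text says challenging; the lack of any safeguard is read from the absence of a stated measure.
- **That the assessors deliver the intervention or attend the key-person meetings.** Only representatives of a multi-professional research group are mentioned.
- **That the on-site folders unmask them.** The cabinet is locked, nothing says the folders are opened before scoring, and a baseline count does not reveal the arm. Scoring without sight of it is good practice for a separate reason: it avoids anchoring on the earlier value.
- **That the two assessors must be balanced over arms to achieve masking.** Balance is a different matter.

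**Conclusion.** The point holds as a design weakness that should be corrected; it is not an error of fact or arithmetic. Under the plan as written, an effort-dependent primary outcome is taken on the units by members of the research group who may know the arm. No partial safeguard is stated, and the planned model cannot remove a shift that follows arm.

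The size is illustrative. With SD 3.5, 49 per group, no clustering and no true effect, an assumed differential of 0.25 to 1 rise gives a two-sided error of about 6% to 29%. With the assumed design effect of 1.45 the range is about 6% to 22%. These figures show how sensitive a trial of this size is to such a shift. They do not show that one will occur, and any unmasked trial with the same inputs would give the same numbers.

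**What to change.** Amend the Blinding section to describe partial masking by the same two assessors:

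1. They are not given the allocation and take no part in staff training, key-person meetings or checks of the flow charts.
2. Visible lists, reminders and bottles are put away before each test visit.
3. Staff and, where feasible, residents are asked not to mention study activities to the assessor.
4. The chair-rise test uses scripted instructions and a fixed rule for what counts as a rise.
5. Follow-up is scored without sight of the baseline count. Because data are already entered after baseline, the baseline sheet can be kept apart from what the assessor uses.
6. Before scoring, the assessor records whether the arm has become known and how.

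Report the frequency and source of unmasking by arm. An analysis restricted to residents whose assessor was still masked should be left out or labelled exploratory. It selects on something that happens after randomisation and is likely to differ by arm, since intervention residents have something to disclose and controls do not.

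The cost is a short amendment and minor test-day logistics, including moving and returning charts that staff use daily. No extra assessor or test is needed. Some unmasking will remain, but it will be less frequent and its extent will be known.
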